### Study Population

All patients presenting with ACC as defined according tot the Tokyo Guidelines [12] to one of the participating hospitals will be assessed for eligibility on presentation. If patients meet the inclusion criteria they will be stratified for hospital and randomised to undergo either LC or PC.

The in- and exclusion criteria are presented in table 2.

**Table 2 T2:** In- and exclusion criteria for eligibility for participation in the CHOCOLATE trial.

Inclusion Criteria	Exclusion Criteria
- Age ≥ 18 - The diagnoses acute calculous cholecystitis defined according to the Tokyo Guidelines: A. Local signs of inflammation: (1) Murphy's sign, (2) Right upper quadrant mass/pain/tenderness B. Systemic signs of inflammation: (1) Fever, (2) elevated CRP, (3) elevated WBC count C. Imaging findings: imaging findings characteristic of acute cholecystitis Definite diagnosis: (1) One item in A and one item in B are positive (2) C confirms the diagnosis when acute cholecystitis is suspected clinically - APACHE-II score ≥ 7 AND ≤ 14 - Written informed consent	- Onset of symptoms > 7 days before first presentation - Already admitted to ICU on presentation - Pregnancy - APACHE-II score ≤ 6 OR ≥ 15 - Acalculous cholecystitis - Decompensated liver cirrhosis - Mental illness prohibiting informed consent

### Randomisation

Patients will be randomly assigned to group A (laparoscopic cholecystectomy) or group B (percutaneous drainage) as shown in the flowchart (Figure 1). Randomisation is done by the study coordinator or primary investigator using an online generator (ALEA 2.2, Academic Medical Centre Amsterdam, the Netherlands https://nl.tenalea.net/amc/ALEA/). Permuted-block randomisation with varying block sizes with a maximum block size of four patients is used to minimize the occurrence of chance imbalance and preserve unpredictability. The sequence of the different blocks is predetermined by an independent programmer and concealed to all investigators. The blocks are generated separately within the different study sites, so stratification according to hospital can be performed.

**Figure 1 F1:**
[figure not shown]
**Flowchart of study outline of included patients**.

### Treatment protocol

All patients presenting with suspected ACC in the emergency department will undergo the standard laboratory work-up and an arterial blood gas analysis. An ultrasound of the abdomen will be performed to confirm the diagnosis. If the findings on ultrasound examination are inconclusive, a contrast enhanced CT-scan of the abdomen will be performed.

When patients are eligible for inclusion and informed consent is obtained randomisation will take place. The allocated treatment has to be performed within 24 hours after randomisation. Figure 1 demonstrates the study outline for included patients.

Group A: Laparoscopic cholecystectomy

LC will be performed by the four trocar technique with transsection of the cystic duct and cystic artery after reaching the critical view of safety as described in the Dutch Guidelines for the treatment of gallstone disease [9]. LC will be performed by a surgeon trained and experienced in laparoscopic surgery defined as > 100 laparoscopic procedures on a yearly basis.

Patients may receive prophylactic antibiotics according to the local hospital protocol.

Antibiotic therapy will not be routinely continued post-operatively unless the performing surgeon has strong indications to do so (such as (imminent) sepsis or hemodynamic instability). In these cases the primary investigator will be notified and the indications have to be well documented.

Group B: Percutaneous drainage

PC will be performed by either ultrasound- or CT-guided percutaneous drainage using an 8.5 French maclock drain. Since there is no consensus in the current literature [9,13] both the transhepatic and transperitoneal routes are allowed and which route is the safest in the individual patient is to be judged by the performing radiologist.

Successful PC is defined as resolution of symptoms and fever and normalization of C-Reactive protein and white blood count. Failure to thrive, defined as clinical deterioration, persisting fever, or increasing infection parameters < 48 hours despite accurate drain position and function will lead to LC.

Patients will be discharged with the drain in place. The drain will be left in situ during a period of three weeks, after which contrast-imaging of the drain will be performed prior to removal to assess whether the drain is still located in the gallbladder and whether there is a patent cystic duct. Patients undergoing PC will not be treated with antibiotics unless the patient is septic with (imminent) hemodynamic instability.

When patients in either group develop an infectious complication antibiotic therapy can be started. All events will be recorded.

### Data collection & follow-up

Each patient will receive an anonymous study number which will be used for the study case-record-forms (CRF) and the database.

On admission baseline patient characteristics including, gender, age, body-mass-index (BMI), comorbidity, previous abdominal surgery, APACHE-II score and duration of symptoms will be documented by the admitting physician or the (local) study coordinator.

The data regarding the procedure including difficulty, duration and complications, will be scored immediately after the procedure by the performing surgeon or radiologist.

During the admission a daily record of the patients including vital signs, laboratory data and complications will be kept.

After discharge the patient will be seen in the outpatient clinic by a surgeon who will complete a questionnaire regarding the patient's clinical condition. The following 11 months the study coordinator will perform the follow up by phone and fill out the CRF regarding complaints, readmissions and interventions.

All entered data will be checked for completion by the study coordinator every three months and missing data will be collected from the participating centers.

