**Methods/Design:**

The CHOCOLATE trial is a randomised controlled, parallel-group, superiority multicenter trial. High risk patients, defined as APACHE-II score 7-14, with acute calculous cholecystitis will be randomised to laparoscopic cholecystectomy or percutaneous cholecystostomy. During a two year period 284 patients will be enrolled from 30 high volume teaching hospitals. The primary endpoint is a composite endpoint of major complications within three months following randomization and need for re-intervention and mortality during the follow-up period of one year. Secondary endpoints include all other complications, duration of hospital admission, difficulty of procedures and total costs.

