### Primary & Secondary endpoints

The primary endpoint is a composite endpoint of all major morbidity, re-intervention and mortality. Table 1 provides an overview of the definitions. Complications occurring during the first 30 days subsequent to randomisation and need for reintervention and mortality during the one year follow-up period will be compared.

**Table 1 T1:** Definitions of the primary endpoint.

Endpoint	Definition
*Complications*	
Intra-abdominal abscess	Fever and/or elevated CRP/WBC and intra-abdominal fluid collection on CT-imaging or ultrasound.
Biliary injury	All injuries of the intra- and extrahepatic biliary ducts including leakage of the biliary tree*.
Bleeding	Drop in haemoglobin level requiring transfusion and/or reintervention.
Pneumonia	Coughing or dyspnoea, radiography with infiltrative abnormalities, elevated infection parameters and positive sputum culture.
Myocardial infarction	Symptomatic elevated cardiac enzymes and abnormalities on electrocardiography or cardiac ultrasound.
Cerebrovascular	(Temporary) loss of function of any body part or sense caused by cerebral ischemia or bleeding, proven on cerebral CT imaging.
Thrombo-embolic	Symptomatic deep venous thrombosis or pulmonary embolism, radiologically proven.
*Need for re-intervention*	Relaparoscopy, laparotomy, ERCP, intervention radiology, readmission
*Mortality*	

CRP - C-Reactive Protein; WBC - White Blood Cell count; CT - computed Tomography; ERCP - Endoscopic Retrograde Cholangiopancreaticography

* Type A: leakage of the minor hepatic ducts or cystic duct. Type B: leakage of common bile duct (CBD) without stricture - Type C: stricture of the CBD without bile leakage - Type D: complete transection of the CBD with or without resection of a part of it [11].

The secondary endpoints include all individual components of the primary endpoint and in addition all minor complications including wound infection, bleeding without need for transfusion or intervention and urinary tract infection, difficulty of cholecystectomy (as scored by VAS 1-10), total length of hospital stay, emergency room visits for related medical problems, re-admissions, duration of hospital and intensive care stay and total (direct and indirect) costs.

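### Only the drainage arm has scheduled contrast imaging inside the complication window, and Table 1 counts biliary leakage without symptoms, so a silent leak has a planned route to detection in that arm alone

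*Protocol article*

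**What the plan says.** **Complication window.** The Primary & Secondary endpoints section counts "Complications occurring during the first 30 days subsequent to randomisation". The Abstract instead describes "major complications within three months following randomization and need for re-intervention and mortality during the follow-up period of one year". Both count complications from randomisation but differ in length. For the other components, the Methods say "need for reintervention and mortality during the one year follow-up period will be compared" and give no starting point for the year.

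**Biliary component.** Table 1 takes in every injury to the bile ducts inside or outside the liver and counts leakage as one. Its footnote grades these as types A to D; type A is a leak from small hepatic ducts or the cystic duct. No symptom, laboratory or treatment threshold is set.

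**PC-only imaging.** Under Treatment protocol, Group B: "The drain will be left in situ during a period of three weeks, after which contrast-imaging of the drain will be performed prior to removal". The stated purposes are to check drain position and whether the cystic duct is open. Group A has no scheduled imaging.

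**Contacts common to both arms** (Data collection & follow-up). In hospital: "During the admission a daily record of the patients including vital signs, laboratory data and complications will be kept". Later: "After discharge the patient will be seen in the outpatient clinic by a surgeon who will complete a questionnaire regarding the patient's clinical condition". Then: "The following 11 months the study coordinator will perform the follow up by phone and fill out the CRF regarding complaints, readmissions and interventions".

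**The concern.** A composite endpoint compares two arms fairly only if an event of a given kind has a similar chance of being found in each. Here one component has no clinical threshold, and one arm has a protocol examination that could reveal it. The examination falls inside the window on either reading of its length.

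The direction matters. The trial is open and aims to prove LC superior. Extra events found only in PC push the result towards that hypothesis, and neither randomisation nor intention-to-treat analysis removes the effect.

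The undated common visit adds to this. If it takes place before the window closes, later complications in LC patients rest on the phone form and on adverse event reports. The phone form's listed content does not match the diagnostic criteria in Table 1.

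**Working it through.** **1. When the drain study falls.** Treatment must take place within 24 hours of randomisation (Treatment protocol), so the drain goes in on day 0-1. Three weeks later is day 21-22, within 30 days and within three months.

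**2. Which Table 1 complications a silent finding could satisfy.**

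| Component | Clinical requirement in Table 1 | Met by a silent imaging finding alone? |
|---|---|---|
| Abscess | Fever or raised CRP/WBC, plus imaging | No |
| Biliary injury or leakage | None | Yes |
| Bleeding | Transfusion or reintervention | No |
| Pneumonia | Symptoms, radiography, infection markers, culture | No |
| Myocardial infarction | Symptomatic | No |
| Cerebrovascular | Loss of function, proven on CT | No |
| Thrombo-embolic | Symptomatic, radiologically proven | No |

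Among the complications, the asymmetry is confined to the biliary component.

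**3. The plan's own figures** (Sample size calculation).
- PC rate: 14.2 + 13.1 + 1 = 28.3%.
- LC rate: 13.6 + 1 = 14.6%.
- Planned difference: 28.3 - 14.6 = 13.7 points.
- Sample size by the uncorrected two-proportion formula, two-sided 5%, 80% power, mean rate 0.2145: n = [1.96 x sqrt(2 x 0.2145 x 0.7855) + 0.8416 x sqrt(0.283 x 0.717 + 0.146 x 0.854)]^2 / 0.137^2 = 140 per arm, as stated.

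**4. Effect on the PC composite.** A silent leak changes a patient's status only if that patient has no other event. Let s be the share of PC patients with a leak seen only on the drain study, independent of other events:
- Added points = s x (1 - 0.283).
- For s = 1%: 0.01 x 0.717 = 0.7 points, or 0.7/13.7 = about 5% of the planned difference.
- If every such leak fell in an otherwise event-free patient, the figure would be 1.0 point. If every one fell in a patient already counted, it would be 0.

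**5. Effect on the false-positive rate.** Assume no true difference, a 14.6% rate in both arms, 140 per arm, and d extra points detected in PC only. Then

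P(reject) = Φ((d - 1.96 SE0)/SE1) + Φ((-d - 1.96 SE0)/SE1),

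with SE0 the pooled and SE1 the unpooled standard error. For d = 0.01 both are about 0.0428 and the result is 5.6%. The share of PC patients needed is d/(1 - 0.146).

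| Extra points in PC (assumed) | Share of PC patients needed | Rejection rate, base 14.6% | Rejection rate, base 21.45% |
|---|---|---|---|
| 1 | 1.2% | 5.6% | 5.5% |
| 2 | 2.3% | 7.5% | 6.9% |
| 3 | 3.5% | 10.5% | 9.2% |
| 5 | 5.9% | about 20% | 16.5% |

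The share column applies to the 14.6% base. None of the values of d comes from the documents.

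**6. End of follow-up.** The visit day V is not given. Eleven months is 334.8 days, so phone follow-up ends at V + 334.8.

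| V (assumed) | Phone follow-up ends | Relative to one year from randomisation |
|---|---|---|
| Day 7 | Day 342 | 23 days short |
| Day 14 | Day 349 | 16 days short |
| Day 21 | Day 356 | 9 days short |
| Day 30 | Day 365 | None short |
| Day 42 | Day 377 | 12 days beyond |

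**The case against.** **The drain study is not a survey of the ducts.** It checks drain position and cystic duct patency, and types A to D do not name leakage from the gallbladder puncture or the drain tract. This stands in part: it narrows what could count and makes a high rate less likely. It does not close the route, because type A covers the small hepatic ducts and cystic duct, a transhepatic drain route is allowed, and Table 1 sets no threshold.

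**Other ascertainment is shared.** Both arms have the daily inpatient record, the clinic visit, the phone follow-up and immediate reporting of (serious) adverse events. Readmission itself counts as re-intervention, so a late complication serious enough to bring a patient back makes the composite positive in either arm. This stands. A reader might infer that complications in general are found unequally. The documents do not support that; the planned difference concerns biliary findings at the drain study.

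**The year need not end early.** A reader might infer that one-year events are cut off because phone follow-up runs from an undated visit. Yet eleven further months within a one-year follow-up imply a visit at about one month, which would close a 30-day window and complete the year. A shortfall needs a visit before about day 30, and the article states no such date. The exact visit date may be in the full protocol.

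**The size is small and hypothetical.** This stands as a limit on severity.

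**Conclusion.** The concern holds as a specific risk of detection bias. As written, the plan can count a clinically silent bile leak as a primary-endpoint event in PC and schedules no means of finding one in LC. The bias would favour LC.

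Its size cannot be derived from the documents. It is about 0.7 points per 1% of PC patients affected under independence (1.0 point at the extreme), against 13.7 planned. At one extra point the false-positive rate barely moves; it becomes material only at several points, for which the documents give no basis. The effect is therefore probably small, but it is cheap to remove.

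Truncation of the one-year period is conditional on an early visit and is not established. What remains on timing is that the article dates no common contact from randomisation and gives the one-year window no starting point.

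**What to change.** 1. In Table 1, count biliary leakage in both arms only if it is clinically manifest by a criterion fixed in advance. The criterion should not rest on whether the leak was treated, since treatment decisions are made unblinded.
2. List findings seen only on the protocol drain study separately, and run a sensitivity analysis that adds them to the composite.
3. Reconcile the 30-day and three-month statements of the complication window. Then date the common surgeon visit from randomisation in both arms, at or after the close of that window.
4. Use the same Table 1 checklist at the visit and in the phone form.
5. State that the one-year period runs from randomisation, and set the last contact at day 365 or later.

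This changes endpoint wording and scheduling only; it adds no imaging and leaves treatment as it is. There are two costs. A rare silent leak no longer counts in the primary composite, though it stays visible in the separate listing and the sensitivity analysis. Some visits would also be booked later: modestly if the window is 30 days, more so if it is three months, in which case the eleven months of phone follow-up would need rewording too.

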### Safety

A data safety monitoring board (DSMB) consisting of three independent members will monitor the safety and efficacy of the trial.

There will be a meeting every six months in which the DSMB will assess unblinded data and evaluate the current status of the trial.

### Adverse events

Adverse events are defined as any undesirable experience occurring to a subject during the study, whether or not considered related to the intervention (i.e. LC or PC).

All participating physicians will inform the study coordinator of all (serious) adverse events ((S)AE) immediately on occurrence.

The primary investigator or study coordinator will list all (S)AE and present these to the DSMB for every 30 randomized patients. All potential (S)AE will be reported to the Central Committee on Research involving Human Subjects ("Centrale Commissie Mensgebonden Onderzoek" [CCMO]) and the accredited medical ethical committee using the online module https://toetsingonline.ccmo.nl.

### Ethics

The CHOCOLATE trial is conducted in accordance with the declaration of Helsinki and the Dutch "Wet Medisch Wetenschappelijk Onderzoek met Mensen" (Medical Research Involving Human Subjects Act).

The study protocol was approved by the "Verenigde Commissies Mensgebonden Onderzoek" (United committees involving human research), the medical ethical committee of the trial coordinating centre at the St Antonius Hospital Nieuwegein on January 20^th ^2011. Secondary approval was obtained from all local ethics committees in the participating centres.

Patients will give oral as well as written informed consent prior to randomisation.

The CHOCOLATE trial is registered in the Dutch Trial Register with identification number NTR2666.

## Statistical aspects

### Sample size calculation

The rates for the primary endpoint: major morbidity, re-intervention and mortality for PC were 6.2, 13.1 and 12.7% respectively in the review and 22.2, 18.5 and 14.8% in our own series. We believe that the 6.2% complication rate in the review is an underestimation of the actual rate, but our own value of 22.2% was based on a retrospective, selected group of patients to undergo PC mostly because of their comorbidity. In these patients the complication rate may very well be higher than in the intended population of the CHOCOLATE trial. We therefore chose to combine both complication rates and use the mean value for our sample size calculation: 14.2%.

Morbidity rates for LC in high risk patients vary greatly in current literature and are mainly based on small, retrospective populations. Mortality rates are described to be around 4.5%. In our own series the complication rate was 13.6% and the mortality rate was 4.3%.

Our endpoint comprises major complications and mortality. These rates cannot be simply added to each other since mortality is in most case associated with major complications. We therefore chose to add intervention rates and complication rates and add up a hypothetical 1% for mortality to ensure that no cases positive for the primary endpoint were missed.

A decrease of the primary endpoint from 28.3% (PC group) to 14.6% (LC group) with power 80%, alpha two-sided 5%, Fisher exact, two proportions, 1:1 randomization can be demonstrated by randomizing 2 × 140 patients (PS Power and Sample Size Calculations, version 2.1.30, February 2003). With an expected loss to follow up of 1%, a total of 284 patients will have to be included in the trial.

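### The planned event rates add a re-intervention term to the PC arm only, and that term supplies 13.1 of the 13.7 points on which the 80% power rests

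*Protocol article*

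**What the plan says.** Under Sample size calculation, the protocol article lists the PC inputs: "major morbidity, re-intervention and mortality for PC were 6.2, 13.1 and 12.7% respectively in the review and 22.2, 18.5 and 14.8% in our own series". It averages the two complication rates, choosing to "combine both complication rates and use the mean value for our sample size calculation: 14.2" (per cent). For LC it reports "In our own series the complication rate was 13.6% and the mortality rate was 4.3" (per cent), and it gives no LC re-intervention rate there or elsewhere.

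Because deaths mostly occur in patients who also have a major complication, the authors do not add the full mortality rates. Their rule is: "We therefore chose to add intervention rates and complication rates and add up a hypothetical 1% for mortality". The design statement that follows is "A decrease of the primary endpoint from 28.3% (PC group) to 14.6% (LC group) with power 80" (per cent), with "alpha two-sided 5%, Fisher exact, two proportions, 1:1 randomization can be demonstrated by randomizing 2 × 140 patients". The total follows: "With an expected loss to follow up of 1%, a total of 284 patients will have to be included in the trial".

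Under Primary & Secondary endpoints, Table 1 defines need for re-intervention as "Relaparoscopy, laparotomy, ERCP, intervention radiology, readmission". The text there says that this component and mortality are compared between the groups over the one-year follow-up.

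**The concern.** The rule has three terms. All three can be seen in the PC figure, but only two in the LC figure. The missing one is re-intervention, a component of the endpoint that Table 1 defines identically for both arms and that includes readmission for any patient.

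The planned effect depends on it. If the two arms are built differently, the planned difference partly reflects how the rates were assembled and not what the treatments are expected to do. The 80% power is then conditional on an LC assumption that the article neither states nor defends. The sponsor, the monitoring board and later readers would judge the trial against a power figure that its own rule does not support.

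**Working it through.** **Inputs** (protocol article, Sample size calculation)

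- PC complications: (6.2 + 22.2)/2 = 14.2%
- PC re-intervention: 13.1% (review), 18.5% (own series)
- LC complications: 13.6%; LC re-intervention: not given
- Mortality allowance: 1.0% in each arm
- 140 per arm, two-sided alpha 5%

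**Step 1: rebuild the event rates**

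- PC: 14.2 + 13.1 + 1.0 = 28.3%, as stated.
- LC: 13.6 + 0 + 1.0 = 14.6%, as stated, but only with a re-intervention term of zero.

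**Step 2: split the planned difference**

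28.3 − 14.6 = 13.7 points, made up of:

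- complications: 14.2 − 13.6 = 0.6
- re-intervention: 13.1 − 0 = 13.1
- mortality: 1.0 − 1.0 = 0

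**Step 3: reproduce the plan's power**

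For two proportions with pooled variance under the null and no continuity correction, power = Φ{[d√n − 1.96 √(2p̄(1−p̄))] / √(p₁(1−p₁) + p₂(1−p₂))}, where d = p₁ − p₂ and p̄ is their mean.

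With p₁ = 0.283, p₂ = 0.146, n = 140 and p̄ = 0.2145: (0.137 × 11.832 − 1.96 × 0.5805)/0.5724 = 0.844, so power = 80.1%. The same formula solved for n gives 140 per arm, and 1% loss gives 142 per arm, or 284. The plan's figures reproduce.

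The article names the Fisher exact test. Exact enumeration of that test gives about 76% at 140 per arm for these same rates. The figures below use the formula that reproduces 140, so they measure the effect of the LC rate alone.

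**Step 4: let LC have a re-intervention increment**

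Let r be the share of LC patients whose only qualifying event is a re-intervention or readmission, so LC = 14.6% + r. The documents give no value, so r is an assumption and is shown as a range. Worked example at r = 5%: p₂ = 0.196, p̄ = 0.2395, d = 0.087; (0.087 × 11.832 − 1.96 × 0.6036)/0.6004 = −0.256, so power = 40%.

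| r | LC rate | Power, PC 28.3% |
|---|---|---|
| 0 | 14.6% | 80% |
| 1% | 15.6% | 73% |
| 2% | 16.6% | 65% |
| 3% | 17.6% | 57% |
| 5% | 19.6% | 40% |

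**Step 5: let the PC rate move as well**

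- With the mean of the two PC re-intervention rates, (13.1 + 18.5)/2 = 15.8%, PC is 14.2 + 15.8 + 1.0 = 31.0%. Power is then 91% at r = 0, 81% at r = 2% and 59% at r = 5%.
- With the same 5 points added to both arms (33.3% against 19.6%), power is about 74%.

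**Step 6: what 2 × 140 can detect**

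At 80% power, the PC rate would have to be 30.8% if LC is 16.6%, and 34.4% if LC is 19.6%.

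**The case against.** The strongest reply is that the composite counts patients, not events. An LC re-intervention in a patient who already has a major complication, or who dies, adds nothing. Table 1 builds in some of this overlap, since a bleed that needs re-intervention is already a complication. A reader might infer from the missing term that 80% power requires no LC patient at all to be re-intervened on or readmitted within a year. The documents do not support that: the 14.6% leaves room for re-interventions among the patients it already counts. This part of the reply stands, and it is why r is defined above as an increment.

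It does not remove the asymmetry. The plan's rule adds the PC complication and re-intervention rates with no allowance for overlap. If overlap justifies zero for LC, it must also reduce the 13.1 points given to PC. In the extreme case where every re-intervention fell in a patient with a complication, PC would be 14.2 + 1.0 = 15.2% against 14.6%.

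Second, the errors may run both ways. PC mortality in the cited sources (12.7% and 14.8%) is well above LC mortality (about 4.5% and 4.3%), yet each arm receives the same 1%. The article does not say whether the 13.1% includes readmissions. Its Background section describes recurrent cholecystitis and interval cholecystectomy after PC at a mean follow-up of eight weeks, whereas the endpoint runs for a year. So holding PC at 28.3% while raising LC shows one side only. This stands, and Step 5 answers it.

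Third, a reader might count as a further error that PC complications are averaged over two sources while PC re-intervention uses the review alone. The article explains the averaging by its belief that the review's complication rate is too low, and the Background section notes that more than half of the studies gave no complication rates. Using 13.1% in place of 15.8% also works against the trial's hypothesis. It is a defensible choice.

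Last, the full protocol may hold a source for the LC figure. The article nevertheless prints the rule, the inputs and the results, and these disagree as printed.

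**Conclusion.** The concern holds. The stated rule is applied in full to PC and without its re-intervention term to LC, no reason is given, and 13.1 of the 13.7 planned points follow from that. The sample size arithmetic itself is sound: 140 per arm and 284 in total do follow from 28.3% and 14.6%. The fault lies in how the 14.6% was built.

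With PC at 28.3%, the 80% is correct only if LC has no re-intervention or readmission beyond the patients already in the 14.6%. How far true power falls short cannot be settled from the documents, because r is unknown. It is 65% at r = 2% and 40% at r = 5% with PC at 28.3%. A higher PC rate offsets part or all of this: at PC 31.0%, r = 2% still leaves 81%. The trial is therefore not shown to be underpowered; its power claim is unsupported by its own rule and sensitive to an undeclared input.

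A reader might go further and infer that a null result would be taken as equivalence. Nothing in the article points that way: it states a superiority aim throughout and plans odds ratios with 95% confidence intervals.

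**What to change.** In the sample size paragraph:

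1. State an LC increment for re-intervention, including readmission, over one year, with its source, and build LC as 13.6 + r + 1.0. Alternatively, justify an increment of zero and treat overlap between complications and re-interventions in the same way for PC.
2. Say whether the 13.1% for PC covers the same events as Table 1, in particular readmission.
3. Restate the power, or the detectable difference, that 2 × 140 delivers over a range of r and of PC rates, using one named calculation method.

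The enrolment target can stay as it is. The cost is a rewritten paragraph and probably a less favourable power statement; no extra patients and no change to trial conduct are needed.

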### Analyses

All patients will be analysed according to the intention to treat approach. Baseline balance will be assessed based on the following patient factors: APACHE-II score, sex, age, duration of symptoms, previous abdominal surgery and previous biliary history. A significant difference (p-value < 0.05) in any of these factors between the two treatment groups will be considered to be an imbalance, the most important factors being APACHE-II score and age. Although we do not expect this to occur, results within the treatment groups will be stratified according to APACHE-II score and age to assure reliable results.

For nominal data the Chi-Square test will be used. For continuous data and counts the independent sample t-test or one-way ANOVA will be used.

In the interim analysis (after one year) the occurrence of the primary endpoint will be compared between the two treatment groups. After the one year follow up of the last patient is completed primary as well as secondary outcomes will be analyzed and compared.

Results will be presented as odds ratios with a corresponding 95% confidence interval. A two-tailed P < 0.05 is considered statistically significant.

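### The 2 × 140 patients give 80% power with an uncorrected chi-square test, not with the Fisher's exact test that the sample size paragraph names (about 76.5%)

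*Protocol article*

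**What the plan says.** The protocol article, under Sample size calculation, gives every input to the calculation. The effect is "A decrease of the primary endpoint from 28.3% (PC group) to 14.6% (LC group"), the power is 80%, and the remaining inputs and the result read: "alpha two-sided 5%, Fisher exact, two proportions, 1:1 randomization can be demonstrated by randomizing 2 × 140 patients". The total is raised to 284 for 1% loss to follow-up.

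Under Analyses, the article names a different test for data of this kind: "For nominal data the Chi-Square test will be used". It does not say whether a continuity correction applies. The significance criterion is a two-tailed P below 0.05.

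**The concern.** Fisher's exact test is conservative for a 2 × 2 table of this size, so it needs more patients than the uncorrected chi-square test for the same power. A sample size that matches the chi-square formula exactly cannot also give 80% power with Fisher's test. Either the label or the stated power is then wrong.

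Two things are at stake. First, readers and the DSMB are told a power that the named test does not have. Second, the two tests can fall on opposite sides of 0.05. With 20 of 140 events against 33 of 140, the uncorrected chi-square p-value is 0.047 and Fisher's is about 0.066. With 22 against 36, the values are 0.039 and 0.055. In an open trial it is better that the document points to one test throughout.

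**Working it through.** **Inputs**, all from Sample size calculation: p₁ = 0.283 (PC), p₂ = 0.146 (LC), two-sided α = 0.05 (z = 1.960), power 0.80 (z = 0.8416), allocation 1:1. Hence the difference is d = 0.137 and the mean rate is p̄ = 0.2145.

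**Step 1: reproduce the 140.** The uncorrected chi-square formula is

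n = [1.960·√(2p̄(1−p̄)) + 0.8416·√(p₁(1−p₁) + p₂(1−p₂))]² / d²

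- √(2 × 0.2145 × 0.7855) = 0.5805; times 1.960 = 1.1378
- √(0.283 × 0.717 + 0.146 × 0.854) = 0.5724; times 0.8416 = 0.4817
- n = (1.1378 + 0.4817)² / 0.137² = 2.6227 / 0.018769 = 139.7, so 140 per arm

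This is the stated number. The allowance for loss also follows: 140 / 0.99 = 141.4, so 142 per arm and 284 in total.

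**Step 2: the usual approximation for Fisher's test**, which adds a continuity correction:

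n′ = (n/4)·[1 + √(1 + 4/(n·d))]² = (139.73/4) × [1 + √1.2089]² = 34.93 × 2.0995² = 154.0, so 154 per arm.

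**Step 3: exact power by enumeration.** For each pair of event counts, take the product of the two binomial probabilities and add up those pairs for which the test gives p ≤ 0.05.

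| Patients per arm | Fisher exact | Chi-square, uncorrected | Chi-square, Yates |
|---|---|---|---|
| 140 | 76.5% | 80.5% | 76.5% |
| 142 (all 284, no loss) | 77.2% | 81.2% | 76.9% |
| 151 | 79.8% | 83.5% | 79.8% |
| 152 | 80.2% | 83.8% | 79.7% |

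Fisher's power is the same to four decimals whether the two-sided p-value adds the less likely tables or doubles one tail.

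**Step 4: could rounding or another formula explain it?** Moving the rates within their rounding (28.25–28.35% and 14.55–14.65%) moves Fisher's power at 140 per arm only between 75.8% and 77.1%. Other two-sided formulas give 137 (unpooled) and 138 (arcsine); one-sided versions give 110 uncorrected and 125 corrected. Of the versions tried, only the two-sided, pooled, uncorrected chi-square gives 140 at the stated rates.

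**Step 5: is the uncorrected test acceptable on type I error?** With a common rate of 0.2145 and 140 per arm, its exact type I error is 4.97%, against 3.6% for Fisher's test. The extra power of the uncorrected test at these rates is not bought by exceeding 5%.

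**The case against.** The strongest reply is that the planned analysis has the power claimed. The primary endpoint is a yes/no composite, the Analyses section names the chi-square test for nominal data, and 140 is the chi-square number. On this view the only fault is the label given to the method in the sample size paragraph. The planning rates themselves are soft (an average of 6.2% and 22.2% for complications, and a hypothetical 1% for mortality), so 3.5 points of power matter little beside them.

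Most of this stands, and it limits the point. A reader might infer that the trial is underpowered, or short of patients because Fisher's test needs about 152 per arm. The document does not support that: it nowhere says that Fisher's test will be used for the analysis. A reader might also infer that the choice of primary p-value is left open between two tests. That too goes too far, because the section that governs the analysis names one test.

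Two things remain. The stated power is not a property of the stated test, and this is a wrong statement rather than a detail left to another document. And the agreement between 140 and the chi-square test holds only without continuity correction. A full protocol or analysis plan may settle that version, but it cannot make 80% the power of Fisher's test at 140 per arm.

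**Conclusion.** The point holds as an inconsistency of modest severity. At 28.3% against 14.6%, two-sided 5% and 140 per arm, Fisher's exact test has about 76.5% power, some 3.5 points below the stated 80%. The test named under Analyses has 80.5% if uncorrected and 76.5% if Yates-corrected. The trial can reach its stated power under its own analysis section, but the planning test and the analysis test differ and should be made to agree.

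This rests on the article's own planning rates taken at face value and on 140 evaluable patients per arm. The interim analysis was left out of the power calculation. The article does not show the output of its sample size program, so how Fisher's test came to be named cannot be told.

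**What to change.** In Sample size calculation, name the uncorrected chi-square test in place of Fisher's exact test. In Analyses, state that the p-value for the primary endpoint comes from the chi-square test without continuity correction. The figures of 140 per arm and 284 in total then stand as printed.

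If Fisher's test is kept as the primary test instead, restate the power as about 76% and change the Analyses section to match.

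Either way the cost is a change of wording in two places. Enrolment and conduct do not change. With 34 patients enrolled when the article was written, the correction could be made before the interim comparison planned after the first year.
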